## Abstract

**Background:**

Cognitive deficits are the core component in persons with schizophrenia which impacts their socio-occupational functioning. Also, cognitive deficits cause significant impairment with the person’s quality of life [3]. Hence, targeting such a pivotal aspect in persons with schizophrenia through suitable interventions is very important. Developed countries have designed various cognitive remediation programs using computers involving high-end software which cannot be generalized to low-resource settings, like India, due to various factors including sociocultural factors, educational standards, and living standards of the patient population. Compensatory cognitive training (CCT) was developed to be “brief, practical, low-tech” and found to be effective in the west [9]. As there are no structured cognitive intervention modules in India, we have adapted the English CCT manual to be used for an urban population in Chennai, India. CCT was found to be feasible in face-to-face group sessions in our setting [12] and is found to be feasible and acceptable as virtual one–one intervention (unpublished data). Therefore, this study aims to evaluate the effectiveness of V-CCT in enhancing cognition and socio-occupational functioning.

**Methods:**

The proposed study will be a multicenter assessor-blinded randomized controlled trial at two clinical sites in Chennai, India. The preparatory phase of the study would include translation of the manual to the local language, recruitment and training of research assistants, and pilot testing using the translated manual. The second phase will be the main randomized controlled trial (RCT), during which a total of 160 persons diagnosed with schizophrenia will be recruited from both sites. After obtaining informed consent, baseline assessments will be conducted on cognition, functioning, self-esteem, and quality of life. Participants will be randomly assigned to either the virtual CCT group or the control group using a computer-generated randomization table. End-line assessments will be conducted 6 weeks after the baseline by research assistants who are blinded to the randomization post-intervention.

**Discussion:**

If V-CCT is found to be effective, it will be available for use in Tamil for persons with schizophrenia, and it will have an effect on their functioning, quality of life, and self-esteem.

**Trial registration:**

The study is registered under Clinical trial registry-India (CTRI), and the registration number is CTRI/2024/04/065267. Registered on April 2024.

### Introduction

#### Background and rationale {6a}

Cognitive deficits are the core component in persons with schizophrenia, impacting their socio-occupational functioning. These deficits affect a person’s ability to lead an independent life, maintain social relationships, get employment, and sustain in them [1]. Cognitive impairments are persistent over time and do not respond to pharmacological treatment [2]. In addition to socio-occupational functioning, cognitive deficits significantly impair a person’s quality of life [3]. Hence, targeting such a pivotal aspect in persons with schizophrenia through suitable interventions is very important.

Cognitive remediation (CR) for schizophrenia, as defined by the Cognitive Remediation Experts Workshop (2010), is a behavioral training-based intervention aimed at improving cognitive processes with the goal of durability and generalization [4]. The literature on cognitive remediation therapy (CRT) demonstrates its effectiveness in improving the social and community functioning in persons with schizophrenia. Based on this evidence, the concept of functional outcome has been reconceptualized as a spectrum: a continuum from neuropsychological performance to social community functioning [5]. A meta-analysis conducted by Wykes et al. reported that cognitive remediation therapy was more effective when patients were clinically stable. Significantly stronger effects on functioning were found when cognitive remediation therapy was provided along with other psychiatric rehabilitation, and a much larger effect was present when a strategic approach was adopted with adjunctive rehabilitation [6].

Developed countries have designed various cognitive remediation programs using computers involving high-end software like NEAR (Neurocognitive and Educational Approach to (Cognitive) Remediation) and CIRCUIT (*C*omputerized *I*nteractive *R*emediation of *C*ognition and *T*hinking *S*kills). These programs utilize compensatory and restorative approaches using the learning principles [7, 8]. However, these programs cannot be generalized to low-resource settings like India due to various factors, including socio-cultural factors, educational standards, living standards of the patient population, budget restrictions, and limited mental health resources. Cognitive interventions are resource intensive, typically requiring the patients to visit the facility for 2–3 sessions per week, often accompanied by a family member. This incurs huge costs from their end, and caregivers are burdened in this process. Moreover, the shortage of mental health professionals exacerbates these challenges and must be kept in mind while developing or implementing these interventions. Considering these limitations, exploring the use of peer support volunteers or persons with lived experience, as well as virtual platforms, is crucial. Hence, it is imperative to develop culturally appropriate, feasible, low-cost, and less resource-intensive manualized cognitive interventions for use in low- and middle-income countries (LAMIC).

### Rationale of the study

Compensatory cognitive training (CCT) was developed to be “brief, practical, low-tech, engaging to clients, and portable enough to be delivered in the community” [9]. It teaches strategies to help clients work around their deficits, linking strategies to goals and roles in the community [10]. A meta-analysis on CCT identified 26 studies across 7 countries and reported a medium effect on functioning and relative durability of effects on cognition [11]. As there are no structured cognitive intervention modules in India, we have adapted the English CCT manual for use in an urban population in Chennai, India. Our study found CCT to be feasible in face-to-face group sessions in our setting [12].

Virtual psychological interventions have been tested and used before and during the pandemic [13–16]. The National Mental Health Survey 2016 also recommends the use of technology to improve services. The SCARF team has piloted virtual one-on-one CCT (V-CCT) and found it to be feasible and acceptable as a virtual intervention. This was delivered using the culturally adapted English version of CCT. According to the unpublished data, 80% of the participants completed all 12 sessions of V-CCT. Pre-post differences were observed in specific domains of cognition. The participants reported benefits such as reduced travel time and cost and made them feel independent as they did not have to rely on their caregivers to attend sessions.

### Objectives {7}

The primary objective of the study is to evaluate the effectiveness of V-CCT in enhancing cognition and socio-occupational functioning among persons with schizophrenia compared to a control intervention. The secondary objective is to assess the effectiveness of V-CCT in improving quality of life and self-esteem.

### Trial design {8}

The proposed study will be a multicenter assessor-blinded randomized controlled trial conducted at two clinical sites in Chennai, India. It will be a parallel group study, with a 1:1 allocation ratio, evaluating superiority of V-CCT over an active control intervention. The intervention sessions for both the groups will be delivered virtually, and participants will join the sessions from home using a tablet/computer.

## Methods: participants, interventions, and outcomes

### Study setting {9}

The study will be conducted in two urban sites:

Schizophrenia Research Foundation (SCARF), Chennai, India.Sri Ramachandra Institute of Higher Education and Research (SRIHER), Chennai, India.

### Eligibility criteria {10}

Participants will be screened and selected at the study sites based on the following inclusion and exclusion criteria.

Inclusion criteria:

❖ Persons diagnosed with Schizophrenia as per ICD 11 classification❖ Aged 18–55 years old❖ Clinically stable patients with a Clinical Global Impressions (CGI) score ≤ 3, receiving outpatient treatment❖ Duration of illness ≥ 2 years❖ Capacity to provide informed consent❖ Ability to communicate in the local language Tamil

Exclusion criteria:

❖ Persons reporting significant impairment in vision and/or hearing that will affect their ability to participate in the trial❖ Current comorbid substance-use disorder❖ Persons with organic brain conditions, intellectual disability, or physical illnesses that impede their ability to participate in the trial❖ History of receiving any interventions targeting cognitive deficits in the past

### Who will take informed consent? {26a}

Researchers who have been trained in good clinical practice and the informed consent procedure will screen the eligible participants for their consent to the study. An information sheet and consent form in the local language will be provided to the participant to read. The researcher will then use a specially designed flipchart to explain the study, including the study process, the concept of randomization, risks, benefits, privacy, and confidentiality. Researchers will address any questions or concerns the participant may have. Participants will be given ample time to review the study details and discuss them with their family members before providing consent. Once the participant’s capacity to consent is ascertained and the participant is ready to consent, they will be asked to sign two consent forms, one of which will be kept by the researcher in a locked filing cabinet and the other one will be given to the participant. Any reasons for refusal to provide consent will be documented.

### Additional consent provisions for collection and use of participant data and biological specimens {26b}

In order to facilitate fidelity assessments, additional consent for audio/video recording of some sessions will be requested from the participants. The study does not include the collection of any biological samples.

## Interventions

### Explanation for the choice of comparators {6b}

We chose to include an active comparator in the control group to ensure engagement and retention in the study as well as to control for the non-specific effects of social interaction and structured activity. While usual care or a waitlist control were considered, we decided that active control with structured sessions (comprising fun games and befriending activities) would allow us to better isolate the specific effects of the V-CCT intervention by maintaining a similar structure, frequency, and duration between groups. The control activities were carefully selected to ensure no direct cognitive enhancement, thereby minimizing any confounding cognitive effects. The control intervention will be delivered by a trained facilitator.

### Intervention description {11a}

The V-CCT intervention, comprising 12 sessions, will be delivered online as a group intervention. Two sessions (1.5 to 2 h per session) per week will be delivered by a trained and certified facilitator. The 12 modules of the CCT intervention cover prospective memory, conversational and task attention, verbal learning and memory, cognitive flexibility, and problem solving.

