### Sample size {14}

A Sample size of 104 participants (52 in each arm) is required based on the outcome indicators of cognitive performance with an effect size of 0.64 between the intervention and control groups, with 90% power and 5% alpha error using R 4.0.3 “pwr.t.test” software. A dropout rate of 50% has been assumed based on previous experiences and studies done using CCT. Therefore, the total number of recruited subjects at both sites will be 156 rounded up to 160 participants in total [22].

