### Implementation {16c}

Participants will be recruited by the research assistants. Once 16 consecutive participants have been recruited, randomization will be done. The allocation sequence will be created by the statistician. Subsequently, the unblinded study coordinator will notify participants of their assigned allocation group.

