## Discussion

This study aims to evaluate the effectiveness of compensatory cognitive training (CCT) in improving cognitive deficits among persons with schizophrenia, compared to an active control intervention. The CCT Intervention will be delivered through virtual platforms in a group format. The study also employs an active control intervention, manualized and translated into Tamil, comprising various fun and befriending activities. The active control intervention helps control for the experience of a group intervention online from home with a facilitator. In addition to assessing improvements in cognition and functioning, the study intends to assess if cognitive interventions can bring a change in quality of life and self-esteem. One of the key strengths of this study is its randomized controlled trial (RCT) design, which effectively controls for baseline confounding factors. Furthermore, it utilizes a superiority study design to test whether the V-CCT intervention out forms the active control arm in improving cognition. While the use of manualized interventions enhances standardization and replicability, there are several limitations to consider. These include digital literacy challenges, and a higher risk of missing data, given the population of persons with lived experience of schizophrenia. In order to address these concerns, we plan to recruit 160 participants, assuming the 50% drop out rate.

We will employ a comprehensive approach to enhance reliability and validity of our study, by including ITT for protocol non-adherence, multiple imputation for missing data, and sensitivity analysis to check robustness of our findings.

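### Both arms are treated in facilitator-led groups, but the sample size assumes independent participants, so 90% power with 104 evaluable holds only if the therapy-group ICC is zero

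*Protocol article*

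**What the plan says.** Intervention description {11a}: "The V-CCT intervention, comprising 12 sessions, will be delivered online as a group intervention". There are two sessions a week, led by a trained facilitator.

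Discussion, on the comparator: "The active control intervention helps control for the experience of a group intervention online from home with a facilitator". The retention section {18b} adds a separate WhatsApp group for each arm and session times that follow the group's agreement.

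Implementation {16c}: "Once 16 consecutive participants have been recruited, randomization will be done". Allocation is 1:1. The number of participants per therapy group, the number of groups and the number of facilitators are not stated.

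Sample size {14}: "A Sample size of 104 participants (52 in each arm) is required based on the outcome indicators of cognitive performance". The inputs are a standardised difference of 0.64, power of 90% and alpha of 5%, and the R function named is pwr.t.test. No ICC or design effect appears. The section then assumes 50% dropout and sets recruitment at 160.

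Statistical methods {20a}: parametric or non-parametric tests are to be chosen after looking at the distributions, under intention to treat, with an effect size and 95% confidence interval. No specific test or model is named, and no term for therapy group or facilitator is mentioned.

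**The concern.** Participants are randomised individually but treated together for 12 sessions with one facilitator and one set of group members. Facilitator skill, group pace and group cohesion can then move the outcomes of a whole group in the same direction. The adverse event section {22} itself cites an earlier participant who dropped out because the pace of the group was too fast.

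When outcomes within a group are positively correlated, each participant carries less independent information than a two-sample t-test calculation assumes. Two things are at stake. First, the stated power is too high for the stated number. Second, if the final analysis also leaves group out, standard errors are too small and a superiority claim is made too easily. The first follows from a calculation the protocol has fixed. The second depends on an analysis it has not fixed.

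**Working it through.** **Inputs from the protocol.** Standardised effect d = 0.64, power 90%, alpha 5% (sidedness not stated), 52 per arm, batches of 16 allocated 1:1, 160 recruited.

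**Assumptions, not in the protocol.** One therapy group per arm per batch: 160/16 = 10 batches, so 10 groups per arm and 20 in all, with 8 randomised per group. With 104 evaluable this leaves m = 104/20 = 5.2 per group. ICC from 0.01 to 0.10, equal in both arms.

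**Step 1: reproduce the plan's figure.** n per arm = 2(1.96 + 1.2816)²/0.64² = 51.3, rounded up to 52 (two-sided). The exact t-test needs 53 per arm, and 52 gives 89.8% power. A one-sided test would need 42, which does not match. The stated 52 is thus the independent-observations figure with no allowance for grouping.

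**Step 2: design effect.** DE = 1 + (m − 1) × ICC. For m = 5.2 and ICC 0.05: 1 + 4.2 × 0.05 = 1.21.

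**Step 3: power.** Noncentrality = 0.64 × √(26/DE), where 26 = 52/2. It is referred to a noncentral t with either 102 df (individuals) or 18 df (20 groups − 2). For ICC 0.05: 0.64 × √(26/1.21) = 2.97.

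**Step 4: type I error if group is ignored.** 2 × [1 − Φ(1.96/√DE)]. For ICC 0.05: 1.96/1.10 = 1.78, giving 7.5%.

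| ICC | DE | Power, 102 df | Power, 18 df | Type I error if group ignored |
|---|---|---|---|---|
| 0 | 1.00 | 89.8% | 87.0% | 5.0% |
| 0.01 | 1.04 | 88.6% | 85.6% | 5.5% |
| 0.02 | 1.08 | 87.4% | 84.2% | 6.0% |
| 0.05 | 1.21 | 83.6% | 80.1% | 7.5% |
| 0.10 | 1.42 | 77.4% | 73.6% | 10.0% |

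The row for ICC 0 shows that about 3 points of each figure in the 18 df column come from the choice of degrees of freedom; the rest comes from the design effect.

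**Step 5: sensitivity to group size and retention.**
- If 8 per group are measured, DE is 1.07 to 1.70 and the type I error of an unadjusted test is 5.8% to 13.3%.
- If all 160 are measured (m = 8), power with 18 df is 96%, 91% and 84% at ICC 0.01, 0.05 and 0.10.
- If half of 160 are lost, as the protocol assumes, 80 remain (m = 4). Power is about 81% at ICC 0 and 75% at ICC 0.05 (71% with 18 df).

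**The case against.** The strongest reply has four parts.

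*The analysis is not fixed.* A reader might infer that the planned tests treat participants as independent and that the confidence intervals are therefore too narrow. The document does not support that as a statement of fact. Statistical methods {20a} names no test, and an analysis plan that is not shown could include a group term. This part of the objection stands, so the type I error figures are conditional. It does not touch the power statement, because the sample size calculation is explicit.

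*The cluster structure is inferred.* The batch of 16 is only the point at which randomisation is done. Groups of about 8, 20 groups and 18 df are a natural reading but are not stated, and the ICC is assumed. This stands too, and it is why ranges are given. At ICC 0.01 the loss is about one point with individual-level df.

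*Batches.* A reader might also infer that ignoring the randomisation batch makes the error bars too narrow. It does not. Each batch is split 1:1, so an effect shared by both arms of a batch cancels in the arm difference. Only correlation within therapy groups inflates the variance of that difference.

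*Recruitment gives a cushion.* Participants who stop treatment are still invited to assessments, so more than 104 may be measured, and 160 measured would absorb a moderate ICC. That is correct if retention is high. It fails under the protocol's own assumption: "A dropout rate of 50% has been assumed based on previous experiences".

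**Conclusion.** The point holds for the sample size. The 52 per arm contains no allowance for group delivery, although both arms are delivered in groups, so 104 evaluable participants give less than the stated 90% power for any positive therapy-group ICC. With about 5.2 evaluable per group and ICC 0.01 to 0.10, power is about 89% to 77% with individual-level df, or 86% to 74% with about 18 group-level df.

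An inflated false-positive rate (about 5.5% to 10%, up to about 13% with 8 per group) would follow only from an analysis that leaves therapy group out. The protocol mentions no such term, but it does not fix an analysis without one either. All these sizes rest on an assumed ICC and an inferred group size. The direction of the power error does not depend on their exact values, provided the ICC is positive.

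**What to change.** In Sample size {14}, state the planned therapy-group size and the number of groups and facilitators, and restate power with DE = 1 + (m − 1) × ICC over a stated ICC range.

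In Statistical methods {20a}, specify a linear mixed model with arm and baseline score as fixed effects, a random intercept for therapy group, and Satterthwaite or Kenward-Roger degrees of freedom.

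Record group and facilitator identifiers for every participant in the database. The session logs and attendance records already planned in Data management {19} probably allow this with little effort.

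Fixed effects for randomisation batch are not needed. With one group per arm per batch they would leave about 20 − 1 − 1 − 9 = 9 df for the arm comparison. Power with 104 evaluable would then fall to about 81% to 68% over the same ICC range.

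The cost is a change of wording, a slightly more complex model, somewhat wider intervals and a lower stated power. No new participant data are needed beyond the identifiers. If the sponsor wants to keep 90% power at a positive ICC, the number analysed must rise: starting from 53 per arm, ICC 0.05 with 5.2 per group needs 53 × 1.21 = 64.1, so 65 per arm or 130 in total, before dropout.

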### Criteria for discontinuing or modifying allocated interventions {11b}

No major adverse events are anticipated due to the interventions. However, in the event that a participant experiences significant psychological distress during a session, the facilitator will pause the session briefly and make sure the participant is able to continue. The participant will be given some time out of the session to recover. If necessary, and the participant continues to feel distressed, they may choose to leave the session. All the participants in the trial will remain in clinical care throughout the study period, and they will be encouraged to seek help from the clinical team.

### Strategies to improve adherence to interventions {11c}

The facilitators will inform participants about the session dates and times. Reminders will be sent to participants both 1 day and 2 h before each session.

### Relevant concomitant care permitted or prohibited during the trial {11d}

During the study period, participants will continue to receive their usual treatment, including pharmacological and psychosocial interventions. However, they will be prohibited from receiving any other cognitive interventions.

### Provisions for post-trial care {30}

The likelihood of participants encountering any harm during the study is extremely low. Should a participant disclose information suggesting an immediate risk to themselves or others, their participation will be immediately discontinued, and a researcher will promptly inform the relevant safeguarding authorities (e.g., clinic). All researchers will be well-versed in safeguarding procedures and will undergo ongoing supervision to ensure adherence to policies and protocols for handling persons who disclose potential risks. The research will be conducted exclusively by trained and proficient researchers experienced in assisting persons dealing with mental health issues. Once the study is completed, if the V-CCT intervention is found to be beneficial, it will be offered to the participants in the control arm.

